## Discussion

Mounting evidence has demonstrated a two-way relationship between obesity and depression as a commonly co-occurring medical situation. Furthermore, both diseases have shown significant links with inflammation. Moreover, metabolic disruptions in obesity can result in increased levels of cortisol, leptin, and insulin, leading to dysregulation of neuroendocrine networks and insulin resistance. In turn, these conditions can lead to further inflammatory effects and worsen depression.

Moreover, the literature has demonstrated that vitamin and mineral deficiency can play a critical role in the pathogenesis of multiple disorders such as obesity and depression with clinical repercussions. Magnesium is one of the most vital elements in the human body and an obvious relationship between circulating magnesium concentrations and depressive symptoms has been shown in some studies. Furthermore, magnesium deficiency is a nutritional problem that results in alterations in cellular function and biological activity of the resident molecules, which may lead to the onset of metabolic disorders associated with inflammatory process. This situation is particularly pronounced in obese individuals with low serum and dietary levels of magnesium.

Additionally, several studies have reported that vitamin D deficiency is related to both depressive symptoms and obesity. Studies of obesity have also demonstrated effects on major central nervous system biomarkers, such as a decrease in BDNF levels in the hippocampus with reversal of the effect following vitamin D administration. SIRT1 is widely located in mammalian cells. Expression and enzymatic activity of SIRT1 are low in many non-communicable diseases, and SIRT1 activation can delay or ameliorate many of these effects. In addition, SIRT1 protects against diet-induced obesity and inflammation as well as obesity-related metabolic dysfunction.

Given the known role of vitamin D and magnesium deficiency in the pathogenesis of many non-communicable disorders, we will test the effects of their co-supplementation in obese women on the readouts of mood and serum levels of BDNF, inflammatory cytokines, and SIRT1.

## Trial status

The present research is at the stage of preparing the material. Protocol version number 2, dated 18 October 2019. Recruitment began on 20 October 2019, and will be completed on 20 December 2020.

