## Methods

### Design

We will conduct an 8-week, double-blind, randomized controlled trial in a factorial design. Participants will be recruited from staff at the Iran University of Medical Sciences through advertisements. The trial will be conducted over 8 weeks to evaluate the effects of vitamin D_3_ (50,000 IU, one dose weekly) and magnesium (250 mg magnesium oxide, one dose daily) in obese women. The output measures will be behavioral readouts of mood, circulating levels of BDNF, cytokines, and SIRT1 (Figs. 1 and 2). The protocol is written in line with the Standard Protocol Items: Recommendations for Interventional Trials (SPIRIT) checklist (Additional file 1).

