### Objectives and hypotheses of the study

The primary objective of the present study is to assess the effects of vitamin D_3_ and magnesium co-supplementation in obese women on readouts of mood, serum levels of 25(OH)-D, magnesium, BDNF, inflammatory biomarkers (hs-CRP, TNF-α, IL-6), and sirtuin 1 levels. For controlling of confounder factors, the study will evaluate anthropometric indices (weight, body mass index, and waist circumference), dietary intake of energy and macronutrients, and physical activity levels in the women at baseline and at the end of the study.

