### Participants

Participants will be 108 obese women. The inclusion criteria will consist of: BMI = 30–40 kg/m^2^; age = 18–50 years; serum 25(OH)D < 30 ng/ml; serum magnesium ≤ 2 mg/dl; no indication of hormonal changes, autoimmune disease, diabetes, hypertension, or renal, hepatic, parathyroid, hormonal, and gastrointestinal disorders; not pregnant, breast-feeding, or menopaused; not taking vitamin D and/or magnesium supplements and other vitamin–mineral supplements or antidepressant drugs; not taking laxative and/or anti-inflammatory medications; and not having had a weight loss of ≥ 3 kg within 2 months leading up to the trial. Exclusion criteria will be less than 90% compliancy with the treatment.

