### Randomization

Randomization to the different treatment arms will be performed using computer-generated random numbers. The 108 participants who meet the criteria will be allocated as such into four treatment groups: 50,000 IU vitamin D soft gel (weekly), plus a 250-mg magnesium tablet (daily); 50,000 IU vitamin D soft gel (weekly) plus a magnesium placebo (daily); vitamin D placebo (weekly) plus a 250-mg magnesium tablet (daily); and a vitamin D placebo (weekly) plus a magnesium placebo (daily). The vitamin D soft gels and magnesium tablets are provided by Zahravi, Iran and Jalinous, Iran, respectively. The placebos for vitamin D and magnesium contained oral paraffin and maltodextrin, respectively, and are supplied by Zahravi, Iran (these were matched in appearance of the corresponding soft gels and tablets). Patients will receive verbal and written counseling on how to consume the supplements and compliance will be evaluated by tablet count every 2 weeks.

For blinding, a person who is not involved in the study protocol will create a randomized list assigning participants to each treatment arm. The soft gels, tablets, and corresponding placebos will be placed into unlabeled identical containers. The study leader will label the containers with participant numbers using the codes generated through the randomization. All investigators and participants will be blinded.

Women who meet the inclusion criteria will be informed completely about the protocol of the study. The ethics committee will review and approve the final study protocol. Each participant will sign the informed consent form.

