### Statistical analysis

Statistical tests of the outcome measures will be performed using SPSS (version 22.0; SPSS Inc., Chicago, IL, USA). The normality of distribution will be examined and confirmed by the Kolmogorov–Smirnov test. All results will be expressed as mean ± SD. Categorical variables will be presented as frequencies and percentages. The chi-square test will be used to test for differences between categorical variables. Baseline mean differences will be tested using one-way analysis of variance (ANOVA). Analysis of covariance (ANCOVA) will be used to identify differences between the four treatment arms at the end of study, adjusting for baseline values and covariates. The comparison of mean values will be done within groups after the intervention period using paired-sample *t* tests. Bonferroni corrections will be used in pairwise comparisons of the values after the intervention. *P* < 0.05 will be considered statistically significant.

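### Entry spans 14 months and follow-up 8 weeks, but season is not among the listed confounders: a modest, cheaply recovered loss of precision for 25(OH)D

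*Protocol article*

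**What the plan says.** All places are in the protocol article.

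- **Trial status:** "Recruitment began on 20 October 2019, and will be completed on 20 December 2020".
- **Design:** "We will conduct an 8-week, double-blind, randomized controlled trial in a factorial design". Each woman therefore contributes one 8-week interval, placed wherever in the 14 months she happens to enter.
- **Participants:** entry requires "serum 25(OH)D < 30 ng/ml".
- **Objectives and hypotheses of the study:** the primary objective covers "readouts of mood, serum levels of 25(OH)-D, magnesium, BDNF, inflammatory biomarkers (hs-CRP, TNF-α, IL-6), and sirtuin 1 levels". The same section sets out what is measured to control confounding: "the study will evaluate anthropometric indices (weight, body mass index, and waist circumference), dietary intake of energy and macronutrients, and physical activity levels". Season, entry date and sun exposure are not in that list, nor anywhere else in the article.
- **Randomization:** "Randomization to the different treatment arms will be performed using computer-generated random numbers". No balancing over calendar time is mentioned.
- **Statistical analysis:** "Analysis of covariance (ANCOVA) will be used to identify differences between the four treatment arms at the end of study, adjusting for baseline values and" further covariates, which are not named. Within-group change is also to be tested with paired t tests.

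**The concern.** In this trial 25(OH)D is an entry criterion, an outcome, and the level that the vitamin D arms are meant to raise. If it follows the seasons (an assumption, since the article is silent on this), an 8-week change in a woman on vitamin D placebo depends on when she entered. Two women with the same baseline, one entering in March and one in October, would be expected to drift in opposite directions. The baseline value cannot tell them apart; the entry date can.

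Two things are at stake. The first is precision: predictable variation stays in the residual and widens the interval for the vitamin D contrast on 25(OH)D, and possibly on the depression score. The second is interpretation: a paired t test within one arm cannot separate treatment change from seasonal change.

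**Working it through.** **1. The window.** 20 October 2019 to 20 December 2020 is 427 days; 427 / 30.44 = 14.0 months. Follow-up is 8 weeks = 56 days.

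**2. The plan's own figure.** With SD 1570.5 ng/ml, 1250.0 ng/ml used as a difference, two-sided α = 0.05 and power 0.80:

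n = 2 × (1570.5 × (1.960 + 0.842) / 1250.0)² = 24.8, rounded up to 25 per group.

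Allowing for attrition the article takes 27, and 27 × 4 = 108. The figure reproduces. It concerns hs-CRP, so nothing below shows it to be wrong.

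**3. Bias and type I error.** Allocation is concurrent across the arms, so an additive seasonal change falls on all of them alike. In a simulation of four arms of 27 with uniform entry over 14 months, the unadjusted contrast had a mean error within 0.003 SD and a type I error of 0.049 to 0.056. With an assumed seasonal term of 0.5 residual SD, its standard error was 0.289 without and 0.273 with season terms (6% larger). At 0.3 residual SD the difference was about 1%.

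**4. Loss of precision for 25(OH)D in the planned ANCOVA.** The documents give no seasonal size, so the following are assumptions: a yearly sinusoid of amplitude A = 3 to 8 ng/ml, even entry over the year, a residual SD of 8 ng/ml at each measurement, and a between-woman SD of 6 ng/ml.

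The 56-day phase shift is 2π × 56/365 = 0.964 rad, with cosine 0.570. Then:

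- variance at each visit: V = 36 + 64 + A²/2
- covariance of baseline and end: C = 36 + 0.570 × A²/2
- ANCOVA residual variance without season terms: V − C²/V
- ANCOVA residual variance with season known: 100 − 36²/100 = 87.0

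| A (ng/ml) | V | C | V − C²/V | SE ratio = √[(V − C²/V)/87.0] |
|---|---|---|---|---|
| 3 | 104.5 | 38.6 | 90.3 | 1.018 |
| 5 | 112.5 | 43.1 | 96.0 | 1.050 |
| 8 | 132.0 | 54.2 | 109.7 | 1.123 |

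Fitting two season terms has its own small cost. With no seasonal effect, the simulation in step 3 gave 0.2731 with the terms against 0.2709 without, a factor of 1.008. Dividing by it gives 1.010, 1.042 and 1.114, that is about 1%, 4% and 11%. A simulation of the planned ANCOVA over the same amplitudes also gives about 1% to 11%.

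The upper end is the sensitive one. If 8 ng/ml is instead read as the SD left after baseline adjustment, season adds at least A²/2 × (1 − 0.570²) = 0.337A². For A = 8 this is 21.6 on 64, an SE ratio of √1.337 = 1.156, or about 15% after the same 1.008 correction.

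**5. hs-CRP.** If season explained 2% or 5% of the variance within the planned SD (assumed), adjusting for it would move power at 25 per group from 80.3% to 81.1% or 82.3%.

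**6. Paired t tests.** The largest 56-day seasonal change is 2A × sin(π × 56/365) = 0.927A, or 2.8 to 7.4 ng/ml for A = 3 to 8. Under even entry a full year cancels, leaving the 427 − 366 = 61 days of the calendar that occur twice. The mean drift is then at most 61/427 × 0.927A = 0.132A, or 0.4 to 1.1 ng/ml. If entry clusters in one season, the mean drift can approach the larger figures.

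**The case against.** The strongest reply is that this is a condensed article. It provides for covariates without naming them, and its confounder list is not said to be the full covariate set. Season may already be in the analysis plan, and the randomisation list may be blocked. That stands, and it is why the point is conditional. It does not dispose of the point: the confounder list is the article's only indication of what the covariates will be, and for a vitamin D trial it omits an obvious non-dietary influence on 25(OH)D.

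It can also be said that seasonal amplitude, residual SD and even entry all come from outside the documents. That is true, so the size is a range under stated assumptions.

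Three stronger readings are tempting and are not supported:

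- **That season biases or shrinks the vitamin D contrast.** An additive shift moves all arms alike. Shrinkage would need a season-by-treatment interaction, for example a smaller gain while background 25(OH)D is rising. That is plausible, but the documents neither show it nor give it a size.
- **That chance seasonal imbalance between arms is a further harm.** It is the same added variance seen another way, and the ordinary standard error already includes it.
- **That error variance rises by 6% to 43%.** This comes from setting the mean square of the raw 56-day change, (0.927A)²/2, against 8². It amounts to fixing the baseline slope at 1, whereas the planned ANCOVA estimates it and so absorbs part of the seasonal variation.

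**Conclusion.** The point holds as a minor one about precision and interpretation. A 14-month entry window, 8-week follow-up and a confounder list without season leave seasonal drift in the residual for 25(OH)D, and possibly for the depression score, unless season is among the unnamed covariates. For 25(OH)D the cost is about 1% to 11% on the standard error of an arm contrast. This rests on a sinusoidal season of 3 to 8 ng/ml, a residual SD of 8 ng/ml and even entry; one alternative reading of that SD takes the top end to about 15%. For hs-CRP the effect is likely smaller. The randomised comparison stays valid, type I error is intact, and 25 per group is not called into question. The within-group paired t tests are more exposed, because they have no concurrent control.

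**What to change.** Before unblinding, prespecify entry date as a baseline covariate in the ANCOVA, either as one sine and one cosine term of the calendar year or as quarter of entry. State that conclusions rest on the between-arm contrasts, with within-group paired results as description only.

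The cost is two or three degrees of freedom. With 108 women, four arms and one baseline term, the residual falls from 103 to 101 or 100. If season turns out not to matter, the loss is about 1% on the standard error. Entry date should be available from the baseline visit, although the article does not say so. Nothing in eligibility, treatment, visits or sample size changes. If season is already among the planned covariates, naming it is enough.

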## Data Availability

Not applicable.
